## Abstract

**Background:**

General practitioners (GPs) frequently order blood tests when they see patients presenting with unexplained complaints. Due to the low prevalence of serious pathology in general practice, the risk of false-positive test results is relatively high. This may result in unnecessary further testing, leading to unfavourable effects such as patient anxiety, high costs, somatisation and morbidity. A policy of watchful waiting is expected to lower both the number of patients to be tested and the risk of false-positive test results, without missing serious pathology. However, many general practitioners experience barriers when trying to postpone blood testing by watchful waiting. The objectives of this study are (1) to determine the accuracy of blood tests in patients presenting with unexplained complaints in terms of detecting pathology, (2) to determine the accuracy of a watchful waiting strategy and (3) to determine the effects of a quality improvement strategy to promote the postponement of blood test ordering by GPs for patients with unexplained complaints.

**Design:**

General practices are randomised over three groups. Group 1 is instructed to order blood tests immediately, group 2 to apply a watchful waiting policy and group 3 also to postpone testing, but supported by our quality improvement strategy. The trial consists of two sub-studies: a diagnostic study at patient level (group 1 versus groups 2 and 3) and a quality improvement study at GP level (group 2 versus group 3). The diagnostic strategy to be used involves of both customary and innovative tests. The quality improvement strategy consists of two small-group meetings and a practice outreach visit. Patient follow-up ends at 12 months after the initial consultation. Primary outcome measures are the accuracy and added value of blood tests for detecting pathology, the effect of a 4-week postponement of test ordering on the blood test characteristics and the quantity of tests ordered. Secondary outcome measures are the course of complaints, quality of life, satisfaction with care, anxiety of patients and practitioners, determinants of physicians' behaviour, health care utilisation and costs.

**Discussion:**

The innovative aspect of this trial is that it combines a clinical-epidemiological study and a quality of care study.

## Background

### Unexplained complaints

'Unexplained complaints' can be defined as: those complaints for which a general practitioner (GP), after clarifying the reason for encounter, taking history and performing physical examination, is unable to establish a diagnosis.[1] This definition reflects a broad continuum of clinical pictures, ranging from complaints of recent onset to more chronic situations in which the physician is convinced that somatic disease is absent. Newly presented unexplained complaints will in most cases be self-limiting, but they can also develop into chronic complaints, or might be the first sign of serious disease.[2] Since GPs are usually the first health care professionals patients present their complaints to, these complaints belong to the particular expertise of GPs, who are used to deal with this type of complaints autonomously, without referring the patients to hospital.

On average, 13% of consultations involve complaints considered unexplained by the GP.[3] Although only a small minority of these lead to chronicity or serious disease, additional diagnostic testing is often done after history taking and physical examination.[4,5]

### Blood test ordering

It has frequently been suggested that immediate test ordering in unexplained complaints is superfluous.[6-8] Since the pretest probability of serious pathology in patients with unexplained complaints is usually low, the risk of false-positive test results is relatively high. This may result in a chain of unnecessary further testing, which in turn might lead to patient anxiety, high costs, somatisation and a risk of serious side effects or even unnecessary morbidity.[9,10] Applying a watchful waiting policy is recommended because the majority of these complaints are expected to be self-limiting. Patients in whom the complaints are not self-limiting will have a higher prior probability of having serious pathology, and the diagnostic accuracy of tests in this selected group is expected to be higher, because of the lower risk of false-positive test results.

We have found only one guideline on blood test ordering for unexplained complaints in general practice. This guideline, issued by the Dutch College of General Practitioners (NHG), recommends an initial watchful waiting strategy. If a complaint persists, it recommends ordering a limited number of tests (glucose, haemoglobin (Hb), erythrocyte sedimentation rate (ESR) and thyroid stimulating hormone (TSH)).[1,11]

However, these test recommendations are based on theory and consensus rather than on evidence. Moreover, in practice, more blood tests are ordered, or the watchful waiting strategy is not followed. Little is known about the accuracy or additional value of diagnostic blood tests or combinations of such tests, in addition to signs, symptoms and environmental and psychosocial factors, for the purpose of discriminating between self-limiting unexplained complaints and pathology. In addition, the accuracy of some newer tests, such as the carbohydrate deficient transferrin (CDT) test for the detection of pathology in patients with unexplained complaints in general practice, is not yet known.[12] Furthermore, several questions concerning the non-diagnostic effects of test ordering, e.g. on patient and doctor anxiety, remain unanswered. Apart from their diagnostic purposes, GPs frequently order tests for more strategic reasons, e.g. to prevent referral to a specialist or to make the psychosocial nature of complaints more acceptable to the patient, thereby anticipating normal blood test results.[11]

### Improvement of test ordering

Though formal evidence is lacking, one can conclude from the high volume of tests ordered by GPs and the low probability of pathology that there is room for improvement to GPs' blood test ordering behaviour for patients presenting with unexplained complaints.[13,14] It is generally accepted that strategies to improve professionals' behaviour need to be developed systematically, based on barriers to and facilitators of the target behaviour.[15] Determinants of blood test ordering by GPs for patients with unexplained complaints include not only a lack of knowledge about the diagnostic value of blood testing but also practice routines, GPs' tolerance of uncertainty, experienced pressure from patients, tactical motives and the perceived need to reassure patients.[11] This means that a strategy aimed at reducing test ordering by professionals should not only focus on improving diagnostic knowledge but also on skills such as dealing with uncertainty and patient pressure and applying alternative modes to reassure patients. The different types of objectives require adequate and tailored methods of instruction, e.g. teaching a skill requires practising rather than lecturing only. Since patients also seem to play a role in the decision process to order tests, it may be valuable to focus a strategy on patients as well, in order to achieve greater effects.

### Objectives of the study

The first objective of the ongoing study presented here is to determine the accuracy of diagnostic blood tests or combinations of such tests and their value, in addition to signs, symptoms and contextual factors, for the purpose of discriminating between self-limiting diseases and serious pathology in patients presenting with unexplained complaints. The second objective is to compare the accuracy of a watchful waiting strategy with that of immediate test ordering. The third objective is to evaluate the effects of a systematically designed quality improvement strategy for GPs, aiming at the postponement of blood test ordering in patients with unexplained complaints.

### Research questions

1. What is the course of complaints that are considered unexplained by GPs over a period of one year?

2. What is the diagnostic accuracy of blood tests, relative to and in addition to combinations of signs and symptoms, for the purpose of discriminating between self-limiting complaints and early stages of pathology in patients presenting with unexplained complaints?

3. What is the cost-effectiveness of a 4-week watchful waiting policy compared to immediate test ordering in patients presenting with unexplained complaints? 'Costs' in this respect include direct medical costs, absence from work and immaterial costs such as patients' uncertainty, satisfaction and quality of life.

4. What is the cost-effectiveness of a systematically developed strategy to improve GPs' test ordering behaviour, compared to merely instructing them to postpone testing?

### Cooperation

The departments of General Practice of the University of Maastricht and of the Academic Medical Center-University of Amsterdam are cooperating in this study. Data collection ended on December 31, 2004. At the time of writing of this protocol article, we are engaged in data cleaning and analysis.

### Ethical approval and informed consent procedure

#### Ethical approval

The medical ethics committees of both the Academic Medical Center-University of Amsterdam and the University Hospital Maastricht have approved the study.

#### Informed consent procedure

GPs hand out written information and an informed consent form to eligible patients. Patients are given the opportunity to read the information and think about participation before signing the consent form. Patients in group 1 are fully informed about the trial. Patients in groups 2 and 3 are kept naive about the possibility of immediate blood test ordering. This is because it is impossible to blind patients for the test group they are in (immediate or postponed blood test ordering). Bias could be caused by selective dropout of patients and by a Hawthorne effect, as patients can be expected to prefer immediate test ordering over a watchful waiting policy. Patients in groups 2 and 3 are told that the study investigates the way their GPs manage patients with unexplained complaints.

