### Clustered randomised clinical trial

Participating general practices are randomised over 3 groups (figure 1). GPs in group 1 are instructed to order blood tests immediately at the first consultation. Those in group 2 are instructed to restrict blood test ordering to patients with complaints persisting after four weeks. GPs in group 3 are also instructed to try and postpone test ordering, but they also participate in a quality improvement strategy that supports them in postponing test ordering for patients with unexplained complaints. The study design includes two sub-studies. The first is a diagnostic study comparing patients from group 1 (immediate test ordering) with patients from groups 2 and 3 (4 weeks of watchful waiting). The second is a quality improvement study, comparing group 2 (instruction to postpone test ordering) with group 3 (instruction to postpone test ordering plus quality improvement strategy) in terms of the actual postponement of test ordering.

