### Procedure

If, after history taking and physical examination, a patient is considered to have unexplained complaints and gives informed consent, the GP enrols the patient in the study. Depending on the GP's study arm, blood test ordering or a 4-week watchful waiting policy is suggested to the patient. All patients are asked to return to the GP if complaints do not disappear within 4 weeks. If patients return, blood tests are ordered for every patient, irrespective of GPs' study arm. This means that patients in group 1 are then tested for the second time and patients in groups 2 and 3 for the first time.

All tests are performed at the regional laboratory, according to local standard operating procedures and using the local reference values.

Patient follow-up ends at 12 months after the initial consultation.

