#### Patients

Patients in group 1 are fully informed about the blood testing options, whereas patients from groups 2 and 3 are kept naive about the possibility of getting blood tests ordered. All patients are blinded for the possibility that their GP is participating in a quality improvement strategy. In our opinion, full blinding is not possible because there is no placebo for blood testing that is feasible and ethically acceptable.

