#### Non-inclusion analysis

A non-inclusion analysis will be performed to check whether included patients are comparable to patients who are eligible but not included.

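### Consent follows practice randomisation and its content differs by arm, so group 1 may enrol different patients from groups 2/3; the non-inclusion analysis should be done by arm

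*Protocol article*

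**What the plan says.** - **Order of events.** Under Clustered randomised clinical trial: "Participating general practices are randomised over 3 groups". Under Procedure, consent is a condition of enrolment and takes place in a practice already allocated: "Depending on the GP's study arm, blood test ordering or a 4-week watchful waiting policy is suggested to the patient". The GPs section under Blinding states that GPs know their allocation.
- **Consent information.** Under Informed consent procedure: "Patients in group 1 are fully informed about the trial". For the other arms: "Patients in groups 2 and 3 are kept naive about the possibility of immediate blood test ordering", and "Patients in groups 2 and 3 are told that the study investigates the way their GPs manage patients with unexplained complaints".
- **Reason given.** The article wants to avoid selective dropout and a Hawthorne effect, "as patients can be expected to prefer immediate test ordering over a watchful waiting policy".
- **Refusal.** The Power calculation section assumes about 50%, as one figure for all arms.
- **Check on selection.** The Non-inclusion analysis section plans "to check whether included patients are comparable to patients who are eligible but not included". Arm is not mentioned.
- **Second description of the information.** The Patients section under Blinding says that "patients from groups 2 and 3 are kept naive about the possibility of getting blood tests ordered".

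**The concern.** Randomising practices balances the populations from which patients are drawn. It does not protect against selection that occurs afterwards, when patients decide whether to take part. The article applies its premise about patient preference to dropout and to awareness of being studied, but not to who consents. On the same premise, a full account that includes immediate testing could draw in more test-seeking patients in group 1 than the partial account does in groups 2/3.

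The contrasts at stake are those of group 1 against groups 2/3:

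- the effect of a four-week postponement on test characteristics (the second primary diagnostic outcome);
- the cost-effectiveness of waiting (research question 3);
- the Table 4 outcomes on satisfaction, anxiety, medical consumption and sick leave.

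The multilevel analysis under Types of analysis deals with correlation within GPs and practices. It does not correct a difference in who enrolled.

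The one stated check contrasts included with non-included patients. The contrast needed here is between included patients of group 1 and those of groups 2/3.

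**Working it through.** **1. The plan's own figures.** These are not in dispute.

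- Patients: 100 / 0.02 = 5000.
- Inclusions per GP per year: 500 × 12 × 3% (midpoint of 1–5%) = 180.
- GPs: 5000 / 180 = 27.8 (article: 27), and 27 / (1 − 0.5) = 54.
- Per group: 5000 / 3 = 1667 (article: about 1700), so 1667 in group 1 against 3333 in groups 2/3.

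The relevant input is the 50% refusal: half of the eligible patients may select themselves out.

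**2. What a check would show.** The article gives no data on preference or on consent by arm, so these inputs are assumptions: a trait (strong preference for testing) in p = 40% of eligible patients, overall consent of 50% in every arm, and eligible patients split 1:2 between group 1 and groups 2/3. Let a1 and a0 be consent with and without the trait.

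- Proportion included: I = p·a1 + (1 − p)·a0
- Trait among included: p·a1 / I
- Trait among non-included: p·(1 − a1) / (1 − I)

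Example with group 1 at 65% / 40% and no selection in groups 2/3:

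- I = 0.4 × 0.65 + 0.6 × 0.40 = 0.50
- Included: 0.26 / 0.50 = 52%
- Non-included: 0.14 / 0.50 = 28%
- Pooled over arms: included (52 + 2 × 40) / 3 = 44%; non-included (28 + 2 × 40) / 3 = 36%

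In the table, consent is with / without the trait. The last three columns give included minus non-included, in percentage points.

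| Consent group 1 | Consent groups 2/3 | Trait among included, group 1 v groups 2/3 | Gap between arms | Pooled | Group 1 | Groups 2/3 |
|---|---|---|---|---|---|---|
| 65 / 40 | 50 / 50 | 52 v 40 | 12 | +8 | +24 | 0 |
| 80 / 30 | 50 / 50 | 64 v 40 | 24 | +16 | +48 | 0 |
| 50 / 50 | 40 / 56.7 | 40 v 32 | 8 | −10.7 | 0 | −16 |
| 55 / 46.7 | 47.5 / 51.7 | 44 v 38 | 6 | 0 | +8 | −4 |
| 60 / 43.3 | 45 / 53.3 | 48 v 36 | 12 | 0 | +16 | −8 |
| 70 / 36.7 | 40 / 56.7 | 56 v 32 | 24 | 0 | +32 | −16 |

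With one-sided selection (first three rows) a pooled check moves but does not say which arm is responsible. With opposite selection (last three rows) it can show nothing. The check by arm shows it in every row. Overall consent is 50% throughout, so consent rates alone would reveal nothing.

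**3. Size.** Assume that patients with the trait differ by 0.5 SD on a patient-reported outcome.

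- Bias: 0.12 × 0.5 = 0.06 SD and 0.24 × 0.5 = 0.12 SD.
- Standard error (SE) without clustering: √(1/1667 + 1/3333) = 0.030 SD.
- Patients per GP: 5000 / 54 = 92.6. Design effect 1 + 91.6 × ICC = 1.92 at an assumed ICC of 0.01, and 5.58 at 0.05.
- SE with clustering: 0.030 × √1.92 = 0.042 and 0.030 × √5.58 = 0.071 SD.
- Ratio: from 0.06 / 0.071 = 0.8 to 0.12 / 0.042 = 2.9 SEs.

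This treats the GP as the cluster. Practices are randomised, and their number is not given; larger clusters would raise the SE further. A larger SE makes the bias less conspicuous but does not shrink it.

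**4. The two descriptions of the information.** Informed consent procedure says that groups 2/3 are not told of immediate testing. The Patients section under Blinding says that they are not told of testing at all. Under Procedure, patients who return are tested in every arm. A reader cannot tell which account groups 2/3 were given.

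**The case against.** The partial account is deliberate, reasoned and ethics-approved, and it aims to limit bias from dropout. Two provisions also weaken the mechanism. The Participants section excludes, in all arms alike, patients for whom the GP feels that waiting would be unacceptable, which may remove some of the strongest test-seekers. The section on watchful waiting allows testing in groups 2/3 when a patient insists, so such patients can stay in those arms. Both are fair points, but the exclusion is applied by a GP who knows the arm, and neither provision equalises the information on which patients consent.

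A reader might infer that the non-inclusion analysis pools the arms and cannot detect the problem. The article does not say so. It is silent on arm, and a condensed article may leave stratification to the full protocol or analysis plan. Even a pooled check would move under one-sided selection, for any measured correlate of preference. Full cancellation needs groups 2/3 to select against test-seekers, and patients unaware of immediate testing have less reason to behave that way.

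A reader might also compare the illustrative bias with the unclustered SE and get two to four SEs. That ignores the clustering for which the article itself plans to allow.

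Finally, the difference between the two descriptions of what groups 2/3 are told can be read as loose wording. Later testing of returning patients contradicts neither, so this part is a clarification.

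**Conclusion.** The concern holds as a risk. Consent comes after randomisation, recruiters know the arm, and the information differs by arm. The article's own premise about preference makes arm-specific entry credible. The documents do not show that the arms in fact differ: no consent rates or baseline data by arm are given.

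The scope is limited to group 1 against groups 2/3. Group 2 and group 3 patients receive the same information, so the quality improvement comparison is not affected. The accuracy of individual blood tests (the first primary outcome) is not itself a contrast between arms.

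The size cannot be derived from the article. The 0.06 to 0.12 SD rests on an assumed 40% trait prevalence, assumed consent by trait and an assumed 0.5 SD difference. The 0.8 to 2.9 SEs rest also on assumed ICCs of 0.01 to 0.05. What does not depend on these inputs is that a check made without regard to arm cannot say where selection occurred, whereas one made by arm can do so for the variables it covers.

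**What to change.** 1. In Non-inclusion analysis, state that included and eligible non-included patients are compared within each arm, and that the included-minus-not-included differences are compared between group 1 and groups 2/3. Use the variables available for non-included patients, such as age, sex and complaint type.
2. Compare baseline features of included patients between group 1 and groups 2/3.
3. Adjust the group 1 versus groups 2/3 comparisons for age, sex, complaint type, education and T0 complaint intensity. Note that T0 self-reports are collected after consent, so the information given may already have influenced them.
4. Acknowledge under Informed consent procedure that information differing by arm is a possible source of selection at entry, and reconcile that section with the Patients section under Blinding on what groups 2/3 are told.

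Data collection has ended, so consent itself cannot be changed. Items 1 to 3 are analysis of data already collected or already planned for, and item 4 is wording. The cost is lower precision of the check by arm. Adjustment cannot remove selection on test preference, which is not a listed variable.

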## Design

### Operationalisation of 'unexplained complaints'

Of the complaints that are considered unexplained by GPs according to the definition drawn up by the Dutch College of General Practitioners (NHG), the following 5 were selected: fatigue, abdominal complaints, musculoskeletal complaints, itch and weight changes. These were selected on the basis of the following criteria: commonly seen unexplained complaints in general practice, frequent ordering of blood tests and the possibility that clinically relevant underlying diseases are detected by blood tests.

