#### Patients

Patients aged 18 years and older, presenting with one of the unexplained complaints mentioned above, who have not consulted their GPs for this complaint in the previous 6 months and who are able to speak, read and write Dutch are eligible to be included in the study. GPs decide to ask patients to participate in the study after history taking and physical examination, so the decision to label the complaints of a patient as unexplained is made entirely by the GPs. Excluded are patients with unexplained complaints for whom the GPs feel that watchful waiting would be unacceptable to them. Patients are asked to participate by their GPs. The GPs are asked to enrol each consecutive eligible patient.

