### Diagnostic intervention at patient level

#### Selection of blood tests

Members of an expert panel including GPs and hospital specialists (n = 20) have been individually asked to propose tests which they regarded as useful diagnostic tools in general practice for each of the 5 complaints. All tests mentioned at least twice were included in a complaint-specific set of tests (table 1). If not already included in the set, the four tests recommended in the NHG guideline (glucose, ESR, TSH and Hb) were added. In addition, iron parameters (transferrin saturation (TS) and ferritin), anti-endomysium and carbohydrate deficient transferrin (CDT) were added as indicators of haemochromatosis, celiac disease and alcohol abuse respectively. These three diseases can lead to unexplained complaints, are frequently missed by GPs according to the literature and should be demonstrable with the above blood tests. The diagnostic accuracy of these tests in patients presenting with unexplained complaints in general practice has, however, not yet been established.[12,17-20]

**Table 1 T1:** Sets of laboratory tests per complaint

	**Fatigue**	**Abdominal complaints**	**Musculo- skeletal complaints**	**Weight changes**	**Itch**
Alkaline Phosphatase (AF)	x	x		x	
Alanine aminotransferase (ALAT)	x	x		x	x
Amylase		x		x	
Anti-endomysium		x		x	
Aspartate aminotransferase (ASAT)	x	x		x	
Bilirubin					x
Erythrocyte sedimentation rate (ESR)	x	x	x	x	x
Carbohydrate-deficient transferrin (CDT)	x	x		x	x
Creatinin kinase (CK)			x		
Creatinin	x	x	x	x	x
C-reactive protein (CRP)		x			
Differentiated leukocyte count	x	x		x	x
Eosinophils					x
Ferritin	x	x	x	x	
Gamma glutamyl transferase (GGT)	x	x		x	x
Glucose	x	x	x	x	x
Haemoglobin (Hb)	x	x	x	x	x
Potassium (K)	x		x		
Latex fixation test			x		
Lactate dehydrogenase (LDH)	x			x	
Leukocyte count	x	x		x	x
Monosticon	x				
Total IgE		x			x
Thyroid stimulating hormone (TSH)	x	x	x	x	x
Transferrin saturation (TS)	x	x	x	x	
Urea					x
Uric acid			x		
**Total number of tests**	**17**	**18**	**11**	**17**	**14**

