### Measurements

All measurement instruments, measurement times and variables are summarised in table 3.

**Table 3 T3:** Instruments and variables.

**Instrument**	**Variables**	**Time points**					**Population**	**Method**
		**T0**	**T1**^#^	**T1.5**^#^	**T6**	**T12**		**- Provision** **- Person who completes questionnaire** **(- Comments)**

GPs' background data	Personal data	x					All GPs	- By mail
	Practice characteristics	x						- GP
	CME	x						
	Laboratory facilities available in practice	x						

Complaint registration form (for each individual type of complaint)	Symptoms	x	x				All patients	- Present in practice
	Signs	x	x					- GP
	Working hypothesis	x	x					
	Degree of unexplainedness	x	x					
	Degree of suspicion of serious pathology	x	x					
	Degree of insecurity of GP	x	x					
	Satisfaction of GP	x	x					

Patients' background data (included in patient questionnaire)	Date of birth	x	x	x	x	x	All patients	- Handed out by GP (T0, T1)
	Country of birth	x	x	x	x	x		- By mail (T1.5-T12)
	Sex	x	x	x	x	x		- Patient
	Marital status	x	x	x	x	x		
	Type of health insurance	x	x	x	x	x		
	Level of education	x	x	x	x	x		

Patient questionnaire	Intensity of complaints	x	x	x	x	x	All patients	- Handed out by GP (T0, T1)
	Course of complaints	x	x	x	x	x		- By mail (T1.5-T12)
	Satisfaction with care	x	x					- Patient
	Anxiety	x	x					
	Quality of life	x	x	x	x	x		
	- RAND 36							
	- Euroqol thermometer							
	Utilisation of health care	x	x	x	x	x		

Test ordering form	Quality of test ordering	x*	x*				All patients	- Present in practice
	Quantity of test ordering	x	x					- GP

Test result form	Test results	x*	x*				All patients	- Laboratory
								- Laboratory staff

Record examination form	Final diagnosis					x	All patients	- Practice/university
	Utilisation of health care					x		- Researcher
	Use of watchful waiting strategy					x		

		**Meeting 1**		**Meeting 2**		**Practice visit**		

Reports of small group meetings	Participation	x		x			All GPs in intervention group	- Meeting room
	Learning effects	x		x				- Researcher

Evaluation forms of small group meetings	Valuation of programme	x		x			All GPs in intervention group	- Meeting room
	Learning effects	x		x				- Researcher
	Suggestion for improvement	x		x				

GP interview in practice	Barriers and facilitators during change					x	All GPs in intervention group	- Practice
	Stages of change					x		- GP

Cost registration	Costs of development and organising of strategy	x		x		x		- University
								- Researcher

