#### Types of analysis

An intention-to-postpone analysis will be performed. Longitudinal comparisons will be made using repeated measurements techniques and multilevel analysis to correct for potential clustering of outcomes in GPs and practices. Barriers to and facilitators of change are analysed qualitatively.

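### Complaint type, recorded at enrolment, has no stated place in the between-arm models, although unblinded GPs enrol five different complaints after allocation

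*Protocol article*

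**What the plan says.** All references are to the protocol article.

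- *Operationalisation of 'unexplained complaints'*: of the complaints that GPs regard as unexplained, "the following 5 were selected: fatigue, abdominal complaints, musculoskeletal complaints, itch and weight changes".
- *Selection of blood tests*, Table 1: the laboratory sets contain 17 tests for fatigue, 18 for abdominal complaints, 11 for musculoskeletal complaints, 17 for weight changes and 14 for itch. Five tests are in every set: ESR, creatinin, glucose, Hb and TSH.
- *Clustered randomised clinical trial*: the first sub-study is "a diagnostic study comparing patients from group 1 (immediate test ordering) with patients from groups 2 and 3". For the other, "The second is a quality improvement study, comparing group 2 (instruction to postpone test ordering) with group 3". Neither description mentions complaint type. Practices are randomised in blocks within two regions, and no other stratum is stated.
- *Participants, Patients*: "the decision to label the complaints of a patient as unexplained is made entirely by the GPs". GPs also leave out patients for whom they feel waiting would not be acceptable. *Blinding* states that GPs know their arm.
- *Types of analysis*: the comparisons use repeated-measurement techniques and "multilevel analysis to correct for potential clustering of outcomes in GPs and practices". No patient-level covariate is named.
- *Measurements*, Table 3: the instrument completed at T0 and T1 is the "Complaint registration form (for each individual type of complaint"), so complaint type is on file for every patient.
- *Primary outcome measures*: the quality improvement study has the quantity of tests ordered. The second diagnostic outcome is the effect of a 4-week postponement on test characteristics.

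**The concern.** The authors treat the five complaints as separate diagnostic problems when choosing tests, so GPs' ordering may well differ between them. If so, the mean number of tests ordered in an arm depends partly on which complaints were enrolled there.

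Randomising practices balances the mix in expectation only if enrolment does not depend on the arm. Here eligibility is judged after allocation by someone who knows the arm, and one exclusion turns on whether waiting seems acceptable. In group 3 that judgement may change. These GPs attend meetings from the start of the trial that deal with barriers to waiting, and they have leaflets and a waiting-room video for patients. Group 2 gets none of this. If acceptability of waiting differs by complaint, the two arms can enrol different mixes. A correction for clustering does not remove such a difference.

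At stake are the estimate for the primary outcome of the quality improvement study and some precision in every between-arm model. For the second diagnostic outcome, a change in pooled test characteristics between T0 and T1 may combine a change within complaints with a change in which complaints are tested. The reader would want to tell these apart.

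**Working it through.** **1. The plan's own figures.** 100 / 0.02 = 5000 patients. 500 × 3% (midpoint of 1–5%) × 12 = 180 per GP per year. 5000 / 180 = 27.8, stated as 27. 27 / 0.5 = 54 GPs. 5000 / 3 = 1667, stated as approximately 1700 per group. These reproduce apart from rounding. They imply 54 / 3 = 18 GPs per group and 1667 / 18 ≈ 93 patients per GP. The article gives no complaint mix, ordering rate, persistence rate or pathology rate by complaint, so every input below not taken from it is an assumption.

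**2. Size of a chance imbalance (group 2 versus group 3).** Design effect = 1 + (1667/18 − 1) × ICC. The 95% imbalance in one complaint's share p is 1.96 × √(2p(1−p) × design effect / 1667).

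| ICC of share (assumed) | Design effect | p = 0.2 | p = 0.4 |
|---|---|---|---|
| 0.01 | 1.92 | 3.8 points | 4.6 points |
| 0.05 | 5.58 | 6.4 points | 7.9 points |
| 0.10 | 10.16 | 8.7 points | 10.6 points |

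**3. Effect on tests ordered.** Assumed: two complaint strata with means of 4 and 6 ordered tests, patient SD 3, GP SD 1, ICC of the share 0.05, 18 GPs per arm, 93 patients each, no true effect; 4,000 simulated trials per cell, analysed on GP means.

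| Systematic shift in mix | Bias = shift × 2 | Simulated bias | False rejection, unadjusted | False rejection, adjusted |
|---|---|---|---|---|
| 0 | 0 | 0.00 | 4.6% | 5.7% |
| 10 points | 0.2 tests | 0.19 | 8.4% | 5.1% |
| 20 points | 0.4 tests | 0.39 | 18.5% | 5.0% |
| 30 points | 0.6 tests | 0.59 | 36.0% | 4.8% |

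The first row shows that chance variation in mix is already carried in the standard error. The other rows show that a systematic shift is not. The adjusted bias is about 0 in every row.

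The adjusted column subtracts the known complaint effect. Estimating it adds little: its standard error from 2 × 18 × 93 = 3348 patients is about 3 / √(3348 × 0.25 × 0.95) = 0.106, which at a 30-point shift adds error of 0.3 × 0.106 = 0.03 tests.

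**4. Precision.** In step 3, the GP-level variance is 1 + 9/93 + 4 × 0.0151 = 1.157 unadjusted and 1.097 adjusted. The standard errors are √(2 × 1.157/18) = 0.359 and √(2 × 1.097/18) = 0.349, a gain of about 3%. A second simulation took any test ordered as the outcome, with ordering assumed at 50% for fatigue and 20% for musculoskeletal complaints, and 9 practices per arm with 180 patients each. It gave standard errors of 0.032 against 0.027, 0.047 against 0.044, 0.030 against 0.027 and 0.046 against 0.044, gains of about 4% to 16%. A 10-point shift there gave an unadjusted bias of about 3 percentage points and an adjusted bias of 0.000 to 0.002.

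**5. Test characteristics at T0 and T1.** Assume sensitivity 0.80, specificity 0.90, two equal strata with pathology rates of 1% and 3% (overall 2%, as in the article), and persistence of 30% and 50% unrelated to disease within a stratum. The mix at T1 becomes 0.5 × 0.3 : 0.5 × 0.5 = 37.5 : 62.5. PPV moves from 14.0% to 15.6% (to 16.3% with rates of 0.5% and 3.5%) with test accuracy unchanged. With equal pathology rates it does not move.

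**6. Can accuracy be split by complaint?** Group 1 would have about 100 / 3 ≈ 33 patients with pathology. At an assumed sensitivity of 0.80 the 95% margin is 1.96 × √(0.16/33.3) ≈ ±14 points. On an assumed mix of 35/25/25/10/5% and equal pathology rates, the 33 divide into about 12, 8, 8, 3 and 2.

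**The case against.** The strongest reply is that this argues from silence. The analysis section of a condensed article has three sentences, covariate lists usually sit in the full protocol or analysis plan, and nothing rules out adjustment. That stands against any claim that complaint type will be ignored: the article states no use of it, which is different. It does not answer the point that a clustering correction alone is the weaker method here, when the variable is on file and adjusting is nearly free.

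A reader might infer that any difference in mix will be taken for an effect. The documents do not support that. Randomisation and a correct multilevel model deal with chance imbalance, and bias needs a systematic shift. None is documented: groups 2 and 3 share the instruction to postpone, the exclusion and the request to enrol consecutive patients. Even a 10-point shift gives a bias below one standard error in both simulations. The planned non-inclusion analysis is a partial safeguard, but as described it sets included against non-included patients and does not compare mix between arms.

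A reader might also infer that the change in mix from T0 to T1 is simply bias. It is not. *Blood test ordering* argues that waiting selects patients whose complaints persist, and the second objective concerns the accuracy of the waiting strategy. A changed mix is part of what waiting does, so standardising it away answers a different question. Step 6 also rules out complaint-specific sensitivity as a primary result.

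**Conclusion.** The point holds as an improvement that should be made, not as a demonstrated error. Five complaints with different test sets enter between-arm comparisons, unblinded GPs select patients after allocation, and clustering is the only correction stated. A systematic shift in complaint mix would bias the group 2 versus group 3 comparison by the shift times the difference in ordering between complaints. Neither factor is given, so the size is unknown. The illustrations run from about 0.2 tests at a 10-point shift to 0.6 at 30 points, if strata differ by 2 tests. Without a systematic shift, adjustment gains precision only, about 3% to 16% of the standard error on the assumptions shown.

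For the second diagnostic outcome, the strategy-level comparison is legitimate as it stands. What is lacking is a supportive analysis that shows how much of a change comes from mix.

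Adjustment for complaint type cannot remove selection of patients within a complaint.

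**What to change.** - State that every between-arm multilevel model, including the primary group 2 versus group 3 comparison of tests ordered, contains complaint type (five levels), age and sex as fixed effects, in addition to the GP and practice levels.
- Report complaint mix by arm at T0 and at T1.
- For the second primary outcome, keep the strategy-level comparison as primary. Add, as supportive only, a complaint-adjusted or mix-standardised comparison of the five tests common to all sets. Use also the group 1 patients retested on return at 4 weeks (*Procedure*), which gives a comparison among patients whose complaints persisted in both arms.
- *Cooperation* says that data collection has ended and analysis is in progress. Record whether these choices were fixed before any arm comparison was seen.

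The cost is a few sentences and six model parameters (four for complaint type, one each for age, if linear, and sex). Complaint type, date of birth and sex are already collected at T0. The supportive analysis is extra work and will be imprecise, given about 33 patients with pathology in group 1.
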